## Abstract

**Abstract:**

**Introduction:**

Type 1 diabetes (T1D) is an autoimmune-mediated disorder caused by the destruction of pancreatic beta cells. Although there is an underlying genetic predisposition to developing T1D, the trigger is multifactorial and likely includes environmental factors. The intestinal microbiome has been identified as one such factor. Previous studies have illustrated differences in the microbiota of people with T1D compared with healthy controls. This study aims to describe the evolution of the microbiome and metabolome during the first year of clinical T1D, or stage 3 T1D diagnosis, and investigate whether there are differences in the microbiome and metabolome of children who present with and without diabetic ketoacidosis. The study will also explore possible associations between the microbiome, metabolome, glycaemic control and beta cell reserve.

**Methods and analysis:**

This prospective cohort study will include children with newly diagnosed T1D and sibling controls (n=100, males and females) and their faecal microbiome will be characterised using shotgun metagenomic sequencing at multiple time points during the first year of diagnosis. We will develop a microbial culture biobank based on culturomic studies of stool samples from the healthy controls that will support future investigation. Metabolomic analysis will aim to identify additional biomarkers which may be involved in disease presentation and progression. Through this initial exploratory study, we aim to identify specific microbial biomarkers which may be used as future interventional targets throughout the various stages of T1D progression.

**Ethics and dissemination:**

This study has been approved by the Clinical Research Ethics Committee of the Cork Teaching Hospitals. Study results will be available to patients with T1D and their families, carers, support networks and microbiome societies and other researchers.

**Trial registration number:**

The clinicaltrials.gov registration number for this trial is NCT06157736.

STRENGTHS AND LIMITATIONS OF THIS STUDYThe inclusion of sibling controls will allow for comparison of the microbiome and metabolome to help identify unique biomarkers at type 1 diabetes (T1D) onset.Longitudinal aspect of this study allows monitoring of the evolution of the microbiome and metabolome over the first year of T1D disease.This is a single-site study.

## Introduction

 The incidence of type 1 diabetes (T1D) has been increasing over the past few decades, especially in young children.^1^,^6^ T1D is caused by autoimmune-mediated destruction of pancreatic beta cells. This leads to a complete deficiency of insulin with affected individuals requiring lifelong exogenous insulin administration to achieve glucose homeostasis. The underlying aetiology of this condition is poorly understood but includes a genetic predisposition with a subsequent presumed environmental trigger^7 8^ that initiates and perpetuates the T-cell-mediated autoimmune process.^9^

Several large cohort studies have identified differences in the oral and faecal microbiome in those with T1D compared with healthy controls and suggest that microbiome composition may have a role in the pathogenesis of T1D.^10^,^14^ The composition of the intestinal microbiota is intimately linked to intestinal permeability and inflammation, providing a plausible causal association with T1D development. Under specific conditions, disturbance in the regular microbiota colonising the intestinal tract can occur, thus contributing to the onset of numerous diseases such as obesity,^15^ rheumatoid arthritis,^16^ non-alcoholic fatty liver disease,^17^ cardiovascular diseases,^18^ inflammatory bowel disease^19^ and psychiatric disorders.^20^ T1D may be among this list of diseases caused, or modulated by changes in the intestinal microbiota, supported by observational studies of children who develop T1D.^21^ Under such conditions, the proliferation of proinflammatory bacteria may occur through interactions with the intestinal epithelium. This interaction triggers the release of cytokines, activating essential inflammatory pathways, thereby heightening morbidity and extending the duration of critical illness.^22^

### The intestinal microbiome through the stages to T1D development

The development of T1D progresses through stages including genetic risk, immune activation, immune response, diabetes-related autoantibody development and the progressive decline in insulin production.^23^ This progression from genetic risk to established T1D can be characterised by four stages.^24^ Stage 1 is the presence of multiple islet autoantibodies. Stage 2 includes the presence of abnormal glucose tolerance. Stage 3 involves hyperglycaemia, and stage 4 is defined as established T1D. Associated microbiome characteristics have been described as early as the immune activation stage. A small study of 10 children with one positive diabetes-related autoantibody (ie, the immune activation stage) demonstrated increased intestinal permeability and distinct differences in their intestinal microbiota compared with healthy controls.^25^ A low abundance of lactate- and butyrate-producing species has also been demonstrated.^26^ These microbiome features also disrupt intestinal epithelial barrier function. The converse appears to be true also, where intestinal microbiomes containing genes that promote the biosynthesis of short-chain fatty acids (SCFAs) and strengthen the intestinal barrier appear to have a protective effect against developing autoimmunity or T1D.^12^

At the time of diagnosis, small case-control studies have demonstrated a reduced Firmicutes/Bacteroides ratio,^27^,^29^ reduced microbial diversity^30^ and higher proportion of non-buyrate-producing lactate-using bacteria^13^ in children with T1D. Lower numbers of specific species of *Clostridium* (clusters IV and XIVa),^10 31^
*Prevotella*^13^ and *Akkermansia*^13^ have also been identified in children with new-onset T1D. Rates of intestinal *Candida* colonisation are also higher in those with new-onset^32^ or established^33^ T1D. Additionally, the oral microbiome has been studied in patients with T1D with significant differences demonstrated between those with T1D and healthy controls.^14^

The intestinal microbiome may represent an important environmental trigger for T1D development. At the genus level, *Bacteroides* are frequently found to be present in higher abundance in the intestine of people with T1D or beta cell autoimmunity.^13 26 29 34 35^
*Bacteroides* species might contribute to the thinning of the intestinal mucus layer, increasing intestinal permeability and inflammation.^35^ Increased intestinal permeability can facilitate bacterial and dietary antigens to translocate into the circulation, promoting systemic inflammation.^21^ However, Cinek *et al* showed that *Bacteroides caccae* was inversely correlated with the onset of beta cell autoimmunity.^36^ Different mechanisms have been proposed to explain the role of *Bacteroides* in T1D. Vatanen *et al* hypothesised that the production of a lipopolysaccharide with immunoinhibitory properties by *Bacteroides dorei* strains in early life alters immune development, contributing to the development of T1D.^37^ The conversion of lactate to butyrate by intestinal bacteria increases mucin synthesis. However, *Bacteroides* species convert lactate to acetate, propionate and succinate instead, reducing mucin synthesis and contributing to the thinning of the intestinal mucus layer.^13^

The progression of T1D is affected by the levels of circulating glutamic acid decarboxylase (GAD) antibodies.^38^ GAD is commonly produced by pancreatic beta cells. It has been suggested that GABA production through the bacterial GAD system can lead to the miseducation of the host immune system, triggering autoimmunity against pancreatic beta cells, via molecular mimicry.^21^ Knowing that GABA production by *Bacteroides* GAD-system is a common trait in the human intestine,^39^ these findings suggest that *Bacteroides* may play a role in T1D progression. *Phocaeicola dorei* and *Phocaeicola vulgatus* were classified as *Bacteroides* until recently,^40^ so most studies investigating *Bacteroides* associations with T1D also include *Phocaeicola* species. Different studies found that *P. vulgatus* and *P. dorei* species were in lower relative abundance in patients with T1D than in control groups.^31 34 41^ However, Davis-Richardson *et al* found that *P. dorei* and *P. vulgatus* dominate the intestinal microbiota of Finnish children before the development of islet autoimmunity, making the role of *Phocaeicola* spp. in the disease unclear.^42^

### Intestinal microbiome and permeability in T1D

The ‘leaky gut’ hypothesis links the microbiome with the pathogenesis of T1D.^43^,^45^ The intestinal microbial ecosystem plays an active role in both immune responses and intestinal barrier integrity.^46^ Increased intestinal permeability is seen in rat models at high risk for developing T1D,^47 48^ and increases in gastric and small intestinal permeability are seen prior to the development of insulinitis and diabetes.^47^ In transgenic mice carrying a T cell receptor for a beta cell autoantigen, antibiotic-induced depletion of the intestinal microbiota can trigger the development of T1D,^49^ suggesting a protective role of the intestinal microbiota. In humans, increased intestinal permeability has been demonstrated through increased mannitol^50^ or lactulose^51^ absorption, or serum zonulin levels^52^ at the time of diagnosis of T1D. Furthermore, children at risk for developing T1D have increased intestinal permeability and distinct differences in their intestinal microbiomes compared with healthy controls.^25^ Gastroenteritis caused by rotavirus can trigger seroconversion in children at risk for developing T1D,^53^ and this mechanism may include microbiome disruption.

### Metabolomic associations with the intestinal microbiome

Although characteristic features of the microbiome have been described in small studies comparing children with T1D and controls, additional information is required to understand the role of the microbiome in this context. Metabolic profiles of taxa present in the microbiome may help investigate microbial functional significance^54^ and possibly lead to the identification of therapeutic targets within microbial metabolic pathways.^55^ There have been limited studies exploring metabolomic profiles in children with T1D, but triglycerides, methionine and phospholipids have been shown to possibly play a role in the seroconversion stage of T1D development.^56^ Following the development of T1D-related autoantibodies in infants, analysis of stool metabolomic profiles in conjunction with microbiome analysis demonstrates a drop in alpha diversity with inflammation-favouring metabolites.^57^ This further supports the hypothesis that the intestinal microbiome represents a potential target in altering the progression of T1D.

In order to elucidate associations between the microbiome and the occurrence and evolution of T1D, establish mechanistic links and identify possible targets for interventions, we plan to initially perform short-read metagenomic sequencing followed by bioinformatic analysis. Additionally, we will establish untargeted metabolomic profiles followed by validation of biomarkers of interest. This correlation with microbiome profiles will establish potential microbial functions linking our observations with associated metabolic activities. Specifically, characteristics of the microbiome at the onset of T1D could potentially be linked to immune^9 58 59^ and microRNA^60^,^62^ markers. The interplay between these markers and the microbiome will further advance our understanding of potential mechanisms underlying any associations identified in this study.

By describing and analysing unique patterns of faecal microbiome biodiversity at the onset of T1D, this study will provide a basis for further interventional studies that aim to halt or modify the trajectory of disease progression. This appears to be a feasible target of future study as there are small but promising studies that have identified the intestinal microbiome as a potential target for intervention in T1D.

Prior studies^25^,^33^ employed microbiome analysis techniques such as real-time quantitative PCR, 16S sequencing and culturing of stool samples to gain insights into microbial changes associated with T1D. A recent study has suggested correlation between the microbiome and T1D progression, and reported an association between C peptide levels and microbial diversity.^63^ The novelty of the present study lies in its longitudinal and in-depth approach, employing short-read shotgun metagenomic sequencing in a large cohort during the early stages of T1D. Enabling the examination of entire genomes, this methodology allows for the comprehensive analysis of both the composition and functionality of the faecal microbiota from the onset of disease diagnosis and throughout the first year. Additionally, culturing of stool samples, in parallel with metagenomic shotgun sequencing, will enable insights into the potential identification and characterisation of essential missing microbes during the first year of T1D progression for potential therapeutic interventions.

Advancing our understanding of the intestinal microbiome in this way may have therapeutic implications. In children with established T1D, prebiotics were associated with increased endogenous insulin production and a possible improvement in intestinal permeability.^64^ Restoring the intestinal microbiome via faecal transplant in adults with new-onset T1D has been shown to delay the decline in beta cell function,^65^ suggesting that modulating the intestinal microbiome in those with newly diagnosed T1D may impact disease progression. Identifying putative therapeutic targets within the microbiome would allow for a more focused approach that could be effective in this population. While these studies provide compelling data in support of an association between the microbiome and T1D, further data are required to identify specific microbiome interventional targets throughout the stages of diabetes progression.

This study is designed to bridge existing knowledge gaps and incorporates a robust methodology with specific strengths, augmenting the significance of its findings. The proposed study’s specimen collection strategy, implemented at various time points over a 1-year period, aims to deepen our comprehension of the temporal dynamics of colonising microbiota and their interactions with host physiology. While multicentre trials capturing sufficient case numbers of T1D cases will offer robust conclusions, this study will offer valuable information on faecal microbiome and metabolome associations with disease progression in new-onset T1D. Subsequent research studies can leverage these findings to explore treatment strategies, potentially offering recommendations for the effective administration of probiotic strains and supplements to enhance faecal microbiota diversity and function for improved outcomes.

### Objectives and outcomes

The primary aim of this study is to describe the evolution of the microbiome and metabolome in children during their first year with stage 3 T1D, compared with their siblings without diabetes.

Secondary objectives and outcomes:

To establish if there are differences in the microbiome or metabolome of children who present in diabetic ketoacidosis (DKA) versus those who present without DKA.To establish if there are differences in the microbiome or metabolome in those presenting with mild, moderate or severe DKA.To establish if there is an association between the microbiome or metabolome and glycaemic control during the first year of diagnosis.To establish if there is an association between the microbiome or metabolome and beta cell reserve 1 year after T1D diagnosis.To establish if there is an association between the microbiome or metabolome at the time of T1D diagnosis and preceding hyperglycaemia.

## Methods and analysis

This study will recruit 50 children at the time of diagnosis and 50 unaffected sibling controls and will employ a prospective cohort study methodology to investigate the faecal microbiome of children with newly diagnosed T1D in the first year of diagnosis. All children with newly diagnosed T1D will be assessed for eligibility for enrolment in this study. Inclusion and exclusion criteria are outlined separately in the recruitment strategy outline. Parents of eligible cases and controls will be approached for consent. If a case does not have siblings, they will still be eligible for recruitment. If a case has multiple siblings, more than one sibling can be recruited as a control. Recruitment will be conducted over a 1-year period. Consent for enrolment for both cases and controls will be obtained during the first hospital visit on diagnosis of the index case. The study started in October 2023 and is planned to finish by September 2026.

At each time point (0, 4, 8, 52 weeks), stool will be collected for microbiome analysis from all cases and controls (n=100). Urine for metabolomics will be collected from all study participants at the same time points. A food frequency questionnaire will be completed by all cases and controls at the first and fourth study visits (0 and 52 weeks, respectively). Clinical data, including insulin dosing, glycaemic control and blood results, will be documented at each visit for cases. Cases will be asked to participate in a mixed meal tolerance test (MMTT) at study visit four (52 weeks). This will quantify stimulated C peptide. This result will help to establish if there is a correlation between microbiome and metabolome evolution and beta cell reserve at 1 year. Shotgun metagenome sequencing will be conducted on faecal samples and urine metabolomic analysis will be employed to detect metabolic biomarkers. The study will explore the impact of the underlying diagnosis and environmental factors. The mode of delivery plays a crucial role in shaping the composition and function of the neonatal microbiome.^66 67^ Caesarean section delivery affects early microbiota transmission from mother to infant and the subsequent priming of the immune system, with delivery-dependent differences early in gut microbiota colonisation continuing through the first year of life.^66 67^ Due to this, we will record the mode of delivery in our data collection with ethical approval to access patient charts and will perform shotgun sequencing to compare cases with age-matched controls from 6 months onwards, should any become available.

In addition, the establishment of a microbial biobank will be achieved based on culturomics of stool samples from healthy sibling controls solely as a source of microbes to develop a microbial culture biobank that will support future investigations. Culturomics is solely performed on faecal samples from healthy siblings, and not index cases, with the hope to culture and preserve beneficial bacterial strains that are present in the healthy microbiome but potentially missing or depleted in individuals with T1D. We hypothesise that the microbiome of sibling controls, which is likely healthier than that of the index cases, may contain key bacterial species involved in immune regulation and metabolic health that are absent or depleted in individuals with T1D. By focusing on healthy controls, we aim to identify beneficial microbial species that may play a protective role in delaying or preventing the onset of T1D. The preservation and study of these strains hold the potential for developing therapeutic targets aimed at slowing the onset and progression of the disease.

### Public and patient involvement

During study development, parents were invited to discuss the study and provide feedback through an online virtual meeting. This input was integrated into the study design prior to finalising the approach.

### Study participation and recruitment of subjects

This is a prospective observational cohort study including children with newly diagnosed T1D and their healthy sibling controls. Participants will be recruited from the diabetes service at Cork University Hospital (CUH). We aim to recruit approximately 50 of these children (cases). Healthy siblings of cases will be eligible to be recruited as controls for the study, and we aim to recruit approximately 50 controls. The inclusion and exclusion criteria are summarised in table 1. The study timeline is shown in table 2.

**Table 1 T1:** Inclusion and exclusion criteria

Cases	Controls
*Inclusioncriteria*
Males and females with newly diagnosed T1D	First-degree family members of cases
Aged between 6 months and 18 years at their first study visit	Do not have T1D
Consent provided by parent/guardian to participate in this study	Aged at least 6 months and no older than 18 years at the first study visit
Age-dependent assent or consent obtained for participants aged 6–18 years	Consent provided by parent/guardian to participate in this study
*Exclusioncriteria*	
Are less than 6 months or older than 18 years at the time of their first study visit	
Individuals who have a known diagnosis of inflammatory bowel disease or another medical condition which the study team deems might interfere with the microbiome	
Individuals with complex medical or behavioural needs that would deem the participant unable to participate in the study	
Have a significant acute or chronic coexisting illness (cardiovascular, gastrointestinal, endocrinological, immunological, metabolic) or any condition which contraindicates entry to the study according to the investigator’s judgement	
Participants who are receiving treatment involving experimental medications	
Have a malignant disease or any concomitant end-stage organ disease	

T1Dtype 1 diabetes

**Table 2 T2:** Study visits

*Cases*				
Visit number	1	2	3	4
Study week	1	4	8	52
Informed consent/assent	X			
Review inclusion/exclusion criteria	X			
Demographics/medical history	X			
Height and weight	X	X	X	X
Clinical data extraction (insulin doses, glycaemic control, blood results)	X	X	X	X
Food frequency questionnaire	X			X
Laboratory tests				
Stool for microbiome analysis	X	X	X	X
Urine for metabolomic analysis	X	X	X	X
Mixed Meal Test for C peptide				X
Serum for HLA-typing				X
*Controls*				
Visit number	1	2	3	4
Study week	1	4	8	52
Informed consent/assent	X			
Review inclusion/exclusion criteria	X			
Demographics/medical history	X			
Height and weight				X
Food frequency questionnaire	X			X
Laboratory tests				
Stool for microbiome analysis	X	X	X	X
Urine for metabolomic analysis	X	X	X	X
Serum for HbA1c measurement				X
Serum for HLA-typing				X
Serum for diabetes autoantibodies				X

### Screening and visit 1

Screening will take place during the case’s admission to hospital following their diagnosis with T1D. After reviewing the inclusion and exclusion criteria, once a participant is deemed eligible, they are then offered participation in the study. The aim of the study and the procedures to be undertaken will be explained to all potential participants and their parents/guardians, and they will be provided with a Patient Information Leaflet (PIL) and an Informed Consent Form (ICF) and an age-appropriate Information Leaflet and Assent Form for the participant if relevant. The researcher will review the information outlined in the PIL and the age-appropriate information leaflet with the parent/guardian and potential participant and answer any questions they might have. If the child and their parents/guardians agree to take part in the study, they will be asked to read and sign the assent form and the ICF, respectively. Participants will receive a signed copy to keep. Demographics and medical history, height and weight measurements will be taken at this visit. A food frequency questionnaire will be completed by cases and controls during this visit. Samples of stool and urine will also be collected from cases and controls at this visit. The date of sampling is recorded. Patient status, including whether or not they were acidotic at the time of sampling, will be noted. Clinical data, including insulin dosing and glycaemic control and blood results of cases, will be documented at this visit. Parents or guardians will also be interviewed regarding their child’s history of medication use. The information pertaining to any medications administered will be documented in the participant’s medical records, when accessible, and in the study’s Case Report Form (CRF).

### Study visits 2 and 3

The second and third study visits will take place when the participant (case) returns to CUH for their routine follow-up appointment with the Diabetes Team approximately 1 and 2 months after T1D diagnosis. At these visits, cases and controls will be asked to provide stool and urine samples to the study team. Clinical data, including insulin dosing and glycaemic control, will be documented. Cases will be examined and height and weight recorded.

### Study visit 4

The fourth study visit will take place approximately 12 months after T1D diagnosis. At this visit, cases and controls will be asked to provide stool and urine samples to the study team. They will also be asked to complete a food frequency questionnaire. Clinical data, including insulin dosing, glycaemic control and blood results, will be documented. Height and weight will be recorded for all study participants. Cases will undergo their MMTT at this visit. If the case opts out of the 2-hour MMTT, they can have a shortened test where a single blood draw is taken at 90 min. If the case does not wish to take part in any MMTT, the results of routine clinical bloods, including fasting glucose and fasting C peptide levels, will be recorded instead. This will help to establish whether there is a correlation between microbiome and metabolome evolution and beta cell reserve. Serum for HLA-typing will be taken at this visit also.

Controls will undergo phlebotomy for HLA-typing, diabetes autoantibodies and HbA1c analysis at this study visit. Parent(s) will be given these results if requested. There will be flexibility in the timing of phlebotomy for controls enrolled in the study. Their blood can be taken at any stage during the study (between study visit 1 and the end of the study) to ensure it is convenient for the family and the control.

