##### Serum for diabetes autoantibodies

Serum will be collected from controls at study visit 4 to look for the presence of diabetes autoantibodies. This test will have been carried out in all cases, as per standard medical practice when first diagnosed with T1D.

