##### Serum for HbA1C

A blood sample will be collected from controls to measure their HbA1C at study visit 4.

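### The published return-of-results rule for sibling controls depends on a parental request and does not single out a diabetes-range HbA1c for unprompted notification

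*Protocol article*

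**What the plan says.** The section Study visit 4 of the protocol article sets out the blood tests for controls: "Controls will undergo phlebotomy for HLA-typing, diabetes autoantibodies and HbA1c analysis at this study visit". The rule on return follows directly: "Parent(s) will be given these results if requested". It covers all three results alike. The same paragraph lets a control's blood be drawn at any point from the first visit to the end of the study, so as to suit the family.

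The sections on the individual tests repeat the sampling but give no action on an abnormal value. For autoantibodies: "Serum will be collected from controls at study visit 4 to look for the presence of diabetes autoantibodies". For HbA1c: "A blood sample will be collected from controls to measure their HbA1C at study visit 4". Screening and visit 1 names an information leaflet and a consent form, but does not say what either contains about returning results.

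**The concern.** Controls enter the study as unaffected siblings of a child with new type 1 diabetes. Their parents have no particular reason to expect an abnormal result, and so may not ask for one. Yet one of the tests, HbA1c, can point to diabetes that nobody has yet recognised.

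The published rule treats that result in the same way as an HLA type: it is available to a parent who asks. What is at stake is the safety of an individual child. A value calling for prompt clinical assessment could sit in the study record while the family does not know of it.

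**Working it through.** No arithmetic applies. The check is a reading of every section where a notification duty could stand, followed by tracing one case through the rules.

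**1. Could entry screening make such a result unlikely to matter?** Table 1 requires that controls not have type 1 diabetes, but no glucose, HbA1c or antibody test at entry is stated. Table 2 schedules the controls' HbA1c only at the last visit, with the flexibility already noted. The study's own HbA1c may therefore be the first test to show a problem.

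**2. Does any other section add a duty to notify?**

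| Section | What it provides | Unprompted notification? |
|---|---|---|
| Screening and visit 1 | Leaflet, consent and assent procedure | Not stated |
| Subject withdrawal/exclusion | A participant whose condition conflicts with the entry criteria may be excluded; withdrawal decisions are documented | Not stated |
| Serum for diabetes autoantibodies; Serum for HbA1C | The tests | Not stated |
| Sample analysis | Where assays are run; HbA1c is run at the recruiting hospital | Not stated |
| Data collection and management | Confidentiality, storage and access | Not stated |
| Ethics and dissemination | Sharing of the study's findings | Not stated |

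**3. Does the result matter on the document's own terms?** In its account of disease stages the article says: "Stage 3 involves hyperglycaemia, and stage 4 is defined as established T1D". That passage does not mention HbA1c. The link, that a diabetes-range HbA1c reflects sustained hyperglycaemia, is ordinary clinical reasoning and not a statement of the article.

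**4. Trace one case.** A control has blood taken and the HbA1c comes back in the diabetes range. If the parents ask, the rule gives them the result. If they do not, the article states no next step: no review of the value, no contact with the family, no referral. The withdrawal section might lead to the child's exclusion from the study, but that concerns study participation and not informing the parents.

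**5. Can the size be given?** The harm would be the chance of a diabetes-range HbA1c in a control multiplied by the chance that the family neither asks nor is told by another route. The article gives neither. The group exposed to the rule is the roughly 50 controls planned. The article also does not say when the assays are run or when results become available, so no length of delay follows from the visit schedule.

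**The case against.** The strongest case on the other side is that this is an omission in a condensed article. Handling of abnormal findings usually sits in the full protocol, the leaflet or the consent form, and none of these is shown. This stands as a limit: nobody can say from the article that families will in fact go untold. It does not dispose of the point, because the article is not silent. It publishes a return rule, makes a request the trigger, and draws no line between a routine value and one needing action.

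A reader might infer that results are returned only on request, or that investigators are barred from speaking first. The sentence supports neither. It promises parents access and need not define the investigators' whole duty. HbA1c is measured at the hospital whose diabetes service recruits the families, so clinicians may well act in practice. That makes silence less likely, but the published rule does not require them to act.

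A reader might also extend the point to autoantibodies, since the article says: "Stage 1 is the presence of multiple islet autoantibodies". That goes too far. Some families prefer not to know antibody status, and whether to disclose it unprompted is a policy choice for the investigators and the ethics committee. An opt-out at consent could not serve families already enrolled unless they were contacted again. A single positive antibody and HLA type raise no objection to return on request.

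The study has ethics approval, and parents' feedback was taken into the design. The article does not say whether either process considered this question.

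**Conclusion.** The point holds for HbA1c alone. The published rule makes return of a control's results conditional on a request, and nothing shown adds unprompted notification of a diabetes-range value. Followed as written, it could leave a family that does not ask unaware of possible undiagnosed diabetes.

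This rests on two assumptions: that the rule as published is the operative one, and that a diabetes-range HbA1c in a child enrolled as healthy needs clinical assessment. The second is hardly open to dispute. The first cannot be checked without the full protocol and consent documents, so confidence is moderate. The size is unquantified for the reasons given above. It is a participant-safety matter that should be put right; no estimate, analysis or sample size depends on it.

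**What to change.** Leave return on request in place for HLA type and autoantibodies, and add to Study visit 4 a sentence to this effect:

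> Each control's HbA1c will be reviewed when the laboratory reports it. A value in the diabetes range (threshold to be specified) will be communicated promptly to the parent(s) without a request, and the child will be referred to the diabetes service.

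Review should be tied to the laboratory report and not to the final visit, because control blood may be drawn at any time. If the full protocol, leaflet or consent form already contains such a provision, a cross-reference is enough.

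If it does not, the cost is a minor ethics amendment, information to families already enrolled (recruitment has begun), and a clinical contact for any affected child. No additional study test is needed, since HbA1c is already measured.
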